**Handling of missing data**

For the analysis of the primary research question missing data is reported as NA and no imputation will be performed. The number of missing data points will be reported for each variable and survey period. A summary of missing variables and effects due to incompleteness is reported in the related publications.

For the analysis of the second and third research questions, applicable outcomes will be imputed using missing Forest imputation.

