An initial invitation letter is sent to 200,000 insured individuals, 50,000 of each of the selected chronic conditions (about 25,000 per sub-cohort). Diabetes type 1 and type 2 are considered jointly as there is no differentiation in the selected PROMs. The patients of all chronic diseases are allocated to groups based on their participation in DMP (DMP or non-DMP group). Prior experiences suggest that around 30% of patients react to invitations to participate in research by their insurer [29-31]. Two-thirds of initial participants are expected to allow follow-up contacts and around 40% of these patients will continue participating in all the follow-up surveys after receiving reminders for each task. Therefore, after accounting for non-participants and participants with no complete survey data we expect a complete data set for 16,000 participants. However, the first research question will investigate response rates as there is no evidence on this population yet.

- 1. STUDY PROCEDURE

Eligible participants will be participating in the study for a maximum of four quarters, starting with the first access of the digital questionnaires followed by quarterly digital surveys split into several tasks. To start the survey, participants register with their study pseudonyms and share personal information, e.g., basic demographics and identification data. Each survey period contains four tasks to be completed by participants defined as sets of questions that each will take five to ten minutes to complete. The participants are invited to answer PROM and PREM surveys.
[figure not shown]

*Figure 1: Study design: Participants’ timeline and tasks*

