All patients who were selected in the identification of study population and participated in the study except for patients who are excluded from the study due to:

- Consent withdrawal

All the analyses will be performed on this population.

1. Outcome Variables

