- Using machine learning predictive models (long-short-term memory deep learning network for time trend classification, random forest, logistic regression, decision tree and/or support vector machine) to identify admission risk in Q3 and Q4 based on PROMs/PREMs in Q1 and Q2

*PRO feedback*

- Mainly: Statistically significant change in at least one of the health care behavior dimensions (see 4.2) and comparison of participants who opened the report vs. those who did not, using logistic regression (change/no change)
  - Physical activity: Shift of participants to a higher category
  - Nutrition: Shift of participants to “More healthy” from any other category
  - Tobacco: Shift of participants to a lower category
  - Alcohol: Shift of participants to a lower category
  - Sleep: Share of stable participants (no significant variation in sleep duration)
- Secondly: Descriptive exploratory analysis of the rates of the following two evaluation dimensions and statistically significant differences in subgroups (see 5.1 and 4.3):
  - Understandability
  - Helpfulness
  - Emotional change

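### Single missForest imputation with no variance correction understates uncertainty for imputed Q2–Q4 PROM/PREM scores, modestly to seriously depending on how much of each wave is missing

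*Protocol*

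**What the plan says.** Protocol section 5.1, under handling of missing data, leaves the primary research question unimputed. For the other two it states: "For the analysis of the second and third research questions, applicable outcomes will be imputed using missing Forest imputation". It does not list which outcomes are applicable, and neither this section nor any other names repeated imputations, pooling or a variance correction.

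The extent of missing data follows from section 2.5. Letters go to 200,000 insured people, and a response of about 30% is assumed. Two thirds of those who respond should agree to be contacted again. Within that group the plan assumes that "around 40% of these patients will continue participating in all the follow-up surveys after receiving reminders for each task". From these rates it concludes: "we expect a complete data set for 16,000 participants".

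Section 3 does not restrict the analysis to complete cases. It takes everyone selected who took part, apart from those who withdraw consent, and adds: "All the analyses will be performed on this population".

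Sections 5.1 and 5.2 then apply t-tests or rank-sum tests, chi-square or exact tests, and linear and logistic regressions at a two-sided 0.05 level. Section 5.2 also reports PROM and PREM change and test–retest consistency over time, and Table 1 describes PROM/PREM value-of-care classes in terms of one standard deviation.

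**The concern.** missForest replaces each missing continuous score with a prediction and returns a single filled data set. A prediction lacks the residual scatter of a real answer, and a single data set cannot show how uncertain the prediction is. A standard test on that data set makes two errors in the same direction: it counts imputed people as full observations, and it uses a standard deviation that is too small.

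For research question 2 this bears on the comparison of DMP with non-DMP members, on subgroup differences in PROM/PREM scores, and on change over time. Nominal 5% tests would reject too often. The loss of scatter also affects descriptive results. Follow-up scores predicted from baseline agree with baseline better than real answers would, so test–retest consistency is inflated. Where a PROM/PREM class depends on an SD distance, the cut-off moves and imputed people are pulled towards the average.

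**Working it through.** **Step 1. Reproduce the plan's figure.** 200,000 × 0.30 = 60,000 initial participants; × 2/3 = 40,000 who allow follow-up; × 0.40 = 16,000 complete. This matches section 2.5. The incomplete among those who allow follow-up number 40,000 − 16,000 = 24,000, or 60%.

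**Step 2. Translate to missingness per wave.** The 60% is the share missing at least one survey, not the share missing in each wave. If each of the 24,000 misses one of three follow-up surveys, average missingness is (24,000 × 1/3)/40,000 = 20%. If each misses all three, it is 60%. Two of three gives 40%. These are averages over Q2–Q4; single waves may lie above or below.

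**Step 3. Standard error and coverage.** Let m be the share missing in a wave and r the correlation between baseline and follow-up score. Both the value of r and the mechanism (missing completely at random) are assumptions, because the protocol gives neither. For a mean filled in by conditional-mean prediction from baseline, up to a common factor:

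- variance reported by the naive analysis: 1 − m + m·r²
- true variance: (1 − r²)/(1 − m) + r²
- SE ratio = √(naive/true); coverage of a nominal 95% interval = 2Φ(1.96 × ratio) − 1

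With r = 0.6 (r² = 0.36):

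| m | naive | true | SE ratio | coverage | coverage for r = 0.4 to 0.8 |
|---|---|---|---|---|---|
| 20% | 0.872 | 1.160 | 0.87 | 91% | 90% to 93% |
| 40% | 0.744 | 1.427 | 0.72 | 84% | 80% to 90% |
| 60% | 0.616 | 1.960 | 0.56 | 73% | 64% to 84% |

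**Step 4. Check by simulation.** In a null two-group comparison of a continuous score with 60% missing:

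- single linear regression imputation (r² about 0.3, n = 2,000, 1,000 runs): type I error 28.3%
- multiple imputation with 20 imputations and Rubin's rules, same runs: 5.6%
- single one-pass random-forest imputation, closer to missForest (R² = 0.29, n = 1,000, 200 runs): 13.5%, with reported SE 0.74 of the empirical one

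The random-forest figure has a simulation standard error of √(0.135 × 0.865/200) = 2.4 percentage points, so it is clearly above 5% and clearly below 28%.

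**Step 5. Standard deviation and test–retest.** The SD of an imputed wave is √(1 − m + m·r²) of its true value: √0.872 = 0.93 at 20% missing and √0.616 = 0.78 at 60%. The covariance with baseline is unchanged, so a true correlation of 0.60 would appear as 0.60/√0.872 = 0.64 and 0.60/√0.616 = 0.76 respectively.

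**The case against.** **Size.** A reader might take 16,000 of 60,000 (27% observed) as the working figure and conclude that intervals are far too narrow throughout. The documents do not support that. The 40% in section 2.5 is completion of all surveys, so per-wave missingness is usually lower. The 27% case also requires imputing follow-up surveys for 20,000 people who did not allow contact. Section 3 keeps them in the analysis population, but nothing says that their follow-up scores count as applicable outcomes. At 20% missing the shortfall in coverage is only about 4 points. The 28% type I error belongs to linear imputation; the random-forest check gave about half that. This part of the objection stands and sets the range reported here.

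**Leakage.** A reader might infer that later admissions or Q3/Q4 answers leak into the model meant to "identify admission risk in Q3 and Q4 based on PROMs/PREMs in Q1 and Q2". The protocol does not say what enters the imputation or how it is ordered relative to model training, and such detail may sit in a statistical analysis plan that is not shown. Admissions come from insurer data and need no survey imputation, and first responders have by definition completed the first survey period. Leakage is possible but not shown.

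**Value-of-care cut-offs.** The unambiguous one-SD cut-offs in section 5.2 are for costs, which are claims data. For PROM/PREM outcomes the text speaks of above or below average, while Table 1 refers to one standard deviation. If the cut-off is the average, a shrunken SD does not move it. The effect on these classes is therefore conditional.

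**Research question 3.** Its main outcomes are category shifts in health behaviour, for which missForest returns a class. The arithmetic above covers continuous scores and gives no figure for these.

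**Safeguards.** Section 5.1 promises to report the effects of incompleteness and to run sensitivity analyses. Neither corrects a standard error. Nor is this detail left for later: the method has been named, and it is the method that causes the problem.

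**Conclusion.** The point holds, as a problem of modest to serious size confined to imputed follow-up survey scores. With r = 0.6 and data missing completely at random, a nominal 95% interval covers about 91% at 20% missing and about 73% at 60% missing; over r = 0.4 to 0.8 the extremes are 93% and 64%. Better prediction reduces the problem. Dropout related to health would add bias that these figures do not include.

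The SD shrinkage inflates test–retest figures, and it affects PROM/PREM classes to the extent that Table 1's SD distance is the rule. Q1 scores and claims-based costs and admissions are little affected. The primary research question is not affected, because it uses no imputation. This should be changed before analysis, but it does not threaten the primary result.

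**What to change.** In section 5.1, replace single missForest imputation with multiple imputation, for example chained equations with random-forest or predictive-mean draws, pooled by Rubin's rules. For mean change in scores, mixed models on the observed data are an alternative. List the outcomes that are imputed, and say whether follow-up scores are imputed for people who did not allow follow-up contact. Classify value of care within each imputed data set and pool the resulting shares.

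As a precaution, state that the admission model imputes Q1 and Q2 scores only from information available by the end of Q2, and does so inside the training data.

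The cost is wording and computing time; no data collection changes.

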**Sensitivity analysis**

Sensitivity analyses will be performed for the outcomes (see primary and secondary outcomes in 4.1 and 4.2).

**Subgroup analysis**

Subgroup analyses will be conducted by all patient characteristic variables under 4.2. Height & weight will be combined to BMI according to WHO standards. Additionally, subgroup analyses will be performed by DMP membership and healthcare utilization. Subgroup analyses cover all study participants as well as analyses of each chronic disease population.

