**Secondary Outcomes**

Value of care:

Value of care delivery is assessed according to the Porter value-based healthcare framework:

Patient-Value = Outcome/Costs

In the analysis, we will firstly focus on the outcome side of the value equation and assess the outcome side based on PROMs and PREMs. The categorization into suspected high-value and suspected low-value care is hence based on PROMs and PREMs. Outcomes higher than average in at least two survey periods are classified as suspected high-value care whereas outcomes lower than average in at least two survey periods are classified as suspected low-value care. Outcomes not included in one of the categories will be separated and excluded from analysis (see Figure 4).

[figure not shown]

*Figure 4: Assessment of Value-Based Healthcare - Outcome dimension*

|  | **PROM – outcome (health)** | **PREM – outcome (responsiveness)** |
| --- | --- | --- |
| **Suspected low-value care** | Maximum one standard deviations above average in at least two survey periods | Maximum one standard deviations above average in at least two survey periods |
| **Suspected high-value care** | Maximum one standard deviations below average in at least two survey periods | Maximum one standard deviations below average in at least two survey periods |
| **Measure-ment** | Separately for health-related quality of life (PROPr index score) & disease-specific health (index score of the disease-specific PROM):   - COPD-related health status - Asthma-related health status - Coronary artery disease-related health status - Diabetes-related health status (for both types) | German responsiveness questionnaire index score |

*Table 1: Assessment of Value-Based Healthcare - Outcome dimensions and measurement*

To cover the cost-side of the value equation as well, we add the health care system utilization. For each of the chronic diseases average treatment costs will be calculated. Costs will cover all healthcare related costs (see 2.6 secondary data). Depending on the deviation from the average participants are classified in the following categories:

- Low costs: More than one standard deviation below average in at least two survey periods
- High costs: More than one standard deviation above average in at least two survey periods
- Inconspicuous costs: Else

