Based on the combination of PROMs, PREMs and health care system utilization measured as costs, a value-based healthcare cube is introduced. PROM and PREM scores function as outcome dimensions and healthcare system utilization as cost dimension. Costs are hence added as new axis inside the framework (see Figure 5).

[figure not shown]

*Figure 5: Assessment of Value-Based Healthcare - Framework*

The newly introduced value-based healthcare cube allows the measurement of high-value and low-value care. Along the previously defined areas of suspected high- and low-value care (see Figure 4 and 5), the cube can be subdivided into 27 segments (see Figure 6). High-value and low-value care will be investigated based on the following criteria:

- High-value indication in both dimensions (high patient-relevant indicators (PROMs/PREMs) **at** low costs) (Figure 6 – dark green area)
- High-value indication in at least one dimension (high patient-relevant indicators (PROMs/PREMs) **or** low costs) (Figure 6 – light green area)
- Low-value indication in at least one dimension (low patient-relevant indicators (PROMs/PREMs) **or** high costs) (Figure 6 – light red area)
- Low-value indication in both dimensions (low patient-relevant indicators (PROMs/PREMs) **at** high costs) (Figure 6 – dark red area)

The value of care dimensions will be summarized into high- versus low-value care as the broad definition and into high two-sided, high one-sided, low one-sided and low two-sided value care as narrow definition. For both categorizations the frequency as well as the variation per subgroups (e.g. region, DMP etc.) will be analyzed.

[figure not shown]

*Figure 6: Assessment of Value-Based Healthcare – Framework distinguishing between high- and low-value care*

*Outcome and experience variation*

Mean change in PROM and PREM-index (sub-)scores overall and per subgroup (see 5.1 and 4.3) per disease area over time:

- Average per survey period
- Consistency over time (test-retest reliability)

Meaningful change / Minimally clinical important difference (MCID) in PROM index (sub-)scores overall and per subgroup (see 5.1 and 4.3) per disease area over time:

- Average per survey period
- Consistency over time (test-retest reliability)

*Hospital admission risk based on PROMs/PREMs and patient characteristics*

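### The value labels that contain the cost axis would be compared across utilization subgroups, although utilization is part of the label

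*Protocol*

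**What the plan says.** Section 5.2 (Secondary Outcomes, Value of care) builds the labels in two steps.

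- The first step uses PROMs and PREMs only and yields the suspected high-value and low-value classes.
- The second step brings in costs: "To cover the cost-side of the value equation as well, we add the health care system utilization". The scope is broad: "Costs will cover all healthcare related costs (see 2.6 secondary data". The cut-offs are "High costs: More than one standard deviation above average in at least two survey periods" and "Low costs: More than one standard deviation below average in at least two survey periods".

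The cube then joins the two: "Based on the combination of PROMs, PREMs and health care system utilization measured as costs, a value-based healthcare cube is introduced". The protocol states the role of each axis outright: "PROM and PREM scores function as outcome dimensions and healthcare system utilization as cost dimension". High costs alone are enough for a low-value indication in one dimension and are required for the two-dimension label. Low costs play the same part for high value.

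On subgroups, 5.2 says of the broad and narrow definitions: "For both categorizations the frequency as well as the variation per subgroups (e.g. region, DMP etc.) will be analyzed". The general rule under Subgroup analysis in 5.1 is: "Additionally, subgroup analyses will be performed by DMP membership and healthcare utilization". It makes no exception for labels that contain costs.

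**The concern.** The outcome of the comparison and the variable that defines the groups share content. If patients are grouped by how much care they used, and the label calls high use (as cost) low value, frequent users will carry more low-value labels even when their reported health and experience match those of infrequent users.

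Section 1.2 asks about value of care in subgroups. A table of cube labels by utilization would look like an answer to that question, and with the expected sample it would almost always be statistically significant. It would mainly restate that costly patients have high costs.

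**Working it through.** **The plan's own figure.** Section 2.5 expects 16,000 complete data sets: 200,000 × 0.30 × 2/3 × 0.40 = 16,000. This reproduces. The protocol gives no figure for the comparison at issue, so its size has to be simulated.

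**Inputs from the protocol.** Four survey periods; cost labels at more than one SD from average in at least two periods; low value as low outcome *or* high costs (at least one dimension), or low outcome *at* high costs (both); two-sided 0.05 (5.1).

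**Assumptions not in the protocol.**
- PROM and PREM are independent of utilization, so any gap is an artefact.
- Within-person correlation is 0.6 for PROM/PREM and 0.5 for cost.
- Costs are normal, or lognormal with log-SD 1.
- Low outcome means more than one SD below average in at least two periods on PROM or PREM. Table 1 words these cut-offs in the opposite direction to the text above it; under the null the direction does not matter.
- Patients are split at the median of the utilization variable; 400,000 simulated patients.

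**Results, frequent versus infrequent half (%).** The correlation is that of the split variable with the person-level cost component.

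| Split variable | Costs | High-cost label | Low value, at least one dimension | Low value, both |
|---|---|---|---|---|
| Same-period cost | normal | 33.9 v 0.0 | 54.8 v 31.6 | 10.7 v 0.0 |
| Same-period cost | lognormal | 17.2 v 0.0 | 43.3 v 31.8 | 5.4 v 0.0 |
| Correlation 0.5 | normal | 25.5 v 8.2 | 49.0 v 37.3 | 8.0 v 2.6 |
| Correlation 0.5 | lognormal | 13.7 v 3.4 | 41.0 v 34.0 | 4.4 v 1.1 |
| Correlation 0.2 | normal | 20.4 v 13.3 | 45.4 v 40.8 | 6.4 v 4.2 |
| Correlation 0.2 | lognormal | 10.7 v 6.5 | 39.1 v 35.9 | 3.4 v 2.1 |
| Correlation 0 | normal | 16.9 v 17.0 | 43.1 v 43.1 | 5.3 v 5.3 |
| Correlation 0 | lognormal | 8.6 v 8.6 | 37.4 v 37.6 | 2.7 v 2.7 |

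Repeat runs move these by a few tenths of a point.

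**Check by hand.** Under independence, P(at least one) = 1 − (1 − p_outcome)(1 − p_cost). For the same-period split with normal costs, the frequent half gives 1 − 0.684 × 0.661 = 0.548 and the infrequent half 1 − 0.684 × 1.000 = 0.316. Both dimensions: 0.316 × 0.339 = 0.107 versus 0. The whole gap comes from p_cost. The outcome-only low share is about 31.6% in both halves throughout, with differences of at most 0.3 points.

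**Other ways to define utilization (low value in at least one dimension).**

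| Split variable | Normal costs | Lognormal costs |
|---|---|---|
| Prior-year level | 53.3 v 33.0 | 43.1 v 31.9 |
| Year-on-year change | 47.4 v 38.9 | 40.0 v 35.0 |
| Within-year change | 43.2 v 43.1 | 37.5 v 37.5 |

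**Chance of a significant result at correlation 0.2.** Power ≈ Φ(z − 1.96), with z = difference / √[p1(1 − p1)/n + p2(1 − p2)/n].
- 8,000 versus 8,000: normal costs z = 0.046/0.00782 = 5.9, power above 99%; lognormal z = 0.032/0.00765 = 4.2, power about 99%.
- One disease cohort, assuming 16,000/4 = 4,000 split into 2,000 versus 2,000: about 84% (normal) and 55% (lognormal). At correlation 0.5 both exceed 99%.

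**High-value mirror.** With normal costs and a same-period split, high value in at least one dimension is 31.6% in frequent versus 54.7% in infrequent users. With lognormal costs at log-SD 1, nobody falls more than one SD below average and the mirror is absent. The mean minus one SD is negative once exp(s²) − 1 > 1, that is s > √(ln 2) ≈ 0.83.

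**The case against.** **The comparison is inferred.** Where the cube labels are analysed, 5.2 names region and DMP, not utilization. This is true. But that list is open-ended, and the rule in 5.1 is general and carries no exception, so the combination is what the plan says as written.

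**The intent may already be right.** Section 1.2 asks for subgroup shares of *suspected* low- and high-value care, which 5.2 bases on PROMs and PREMs alone, and names utilization as a comparator for ePROM and ePREM results. This supports the proposed remedy, but nothing in 5.1 or 5.2 carries the distinction over to the cube labels.

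**Utilization need not be same-period cost.** Section 1.1 speaks of frequent and infrequent users, 1.2 of changes in frequency of use, and 2.5 makes utilization a sampling stratum, which must be measured before invitation. This stands and limits the point. A reader might infer that any excess of low value in frequent users is true by construction. The documents do not support that, because they fix neither the metric nor the time window. With prior-year level, the gap reflects persistence of cost between separate claims windows, an empirical association and not an identity. With within-year change there is no gap. A real outcome difference in the other direction could also offset the gap in the one-dimension label.

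**It is definitional.** Section 5.2 defines value as outcome divided by costs, so at equal outcomes costlier care is lower value. As description this is correct. It is also why the table would add nothing on research question 2.

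**A mirror effect on high value** might be inferred too. It depends on the cost distribution and disappears when costs are skewed enough.

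**Conclusion.** The point holds in limited form. Sections 5.1 and 5.2 together call for a comparison that is circular for the cube, broad and narrow labels. It is fully mechanical for same-period cost or utilization and partly built in, according to correlation with study-period costs, for prior-year level or visit frequency. Under the assumed null, the artefact in low value (at least one dimension) runs from about 3 to 5 percentage points at correlation 0.2 (39.1 − 35.9 = 3.2; 45.4 − 40.8 = 4.6) to about 12 to 23 points on a same-period split (43.3 − 31.8 = 11.5; 54.8 − 31.6 = 23.2). These sizes rest on the assumed cost distributions and correlations; the protocol supplies neither. The outcome-only suspected classes are unaffected. This concerns a secondary analysis and is a cheap improvement, not a fault in the primary outcome.

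**What to change.** State in 5.1 and 5.2 that healthcare utilization is a subgroup variable for PROM and PREM scores and for the outcome-only suspected value classes, and is not used for the cube, broad or narrow value labels, which contain the cost axis. If a display by utilization is wanted, report the outcome axis and the cost axis separately.

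The cost is one sentence and one set of tables dropped. What section 1.2 asks for by utilization is kept.
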